## Abstract

**Background:**

Critical illness is a major ongoing health care burden worldwide and is
associated with high mortality rates. Sodium-glucose cotransporter-2
inhibitors have consistently shown benefits in cardiovascular and renal
outcomes. The effects of sodium-glucose cotransporter-2 inhibitors in acute
illness have not been properly investigated.

**Methods:**

DEFENDER is an investigator-initiated, multicenter, randomized, open-label
trial designed to evaluate the efficacy and safety of dapagliflozin in 500
adult participants with acute organ dysfunction who are hospitalized in the
intensive care unit. Eligible participants will be randomized 1:1 to receive
dapagliflozin 10mg plus standard of care for up to 14 days or standard of
care alone. The primary outcome is a hierarchical composite of hospital
mortality, initiation of kidney replacement therapy, and intensive care unit
length of stay, up to 28 days. Safety will be strictly monitored throughout
the study.

**Conclusion:**

DEFENDER is the first study designed to investigate the use of a
sodium-glucose cotransporter-2 inhibitor in general intensive care unit
patients with acute organ dysfunction. It will provide relevant information
on the use of drugs of this promising class in critically ill patients.

ClinicalTrials.gov registry NCT05558098

## INTRODUCTION

Critical illness is a major global challenge, with mortality rates after intensive
care unit (ICU) admission reaching as high as 22%, according to international
estimates.^(1)^ Despite this
alarming issue for health care systems, no specific therapy has yet been shown to
improve outcomes in unselected patients with acute organ dysfunction in the ICU.

Sodium-glucose cotransporter-2 (SGLT2) inhibitors have demonstrated a consistent
reduction in cardiovascular and kidney outcomes in several randomized clinical
trials (RCTs) across a range of clinical settings, including type 2 diabetes
mellitus,^(2)^ heart failure
with reduced and preserved ejection fraction,^(3-6)^ acute heart
failure,^(7)^ and chronic
kidney disease.^(8,9)^ Some of the postulated effects of this drug
class^(10)^ may also
positively impact multiple deleterious pathways of acute illness and protect against
organ injury and failure. Plausible mechanisms that may be involved-particularly in
patients with sepsis^(11)^- include
improved metabolic efficiency^(12,13)^ and endothelial
function,^(14)^ inhibition
of pro-inflammatory pathways^(15)^
and sympathetic activity,^(16)^
decreasing production of reactive oxygen species,^(17)^ and increased erythropoietin
production.^(18)^
Experimental animal models of acute injury provide data that support the existence
of an overlap between the effects of SGLT2 inhibitors and protection against organ
dysfunction. Sodium-glucose cotransporter-2 inhibition prevented renal injury and
reduced biomarkers of systemic inflammation^(19)^ and pathological findings of lung injury^(20)^ in lipopolysaccharide-induced
inflammation models.

In humans, the DARE-19 trial^(21)^
provided pivotal information to support the use of SGLT2 inhibitors in major acute
illness; dapagliflozin numerically reduced the event rates of the coprimary
prevention outcome (a composite of new or worsening organ dysfunction or death) in
hospitalized COVID-19 patients when compared with placebo. Although the results of
the trial failed to meet statistical significance for the efficacy outcome, the use
of dapagliflozin was well tolerated, associated with a low rate of diabetic
ketoacidosis, and did not lead to an increase in serious adverse events despite
previous concerns.^(22)^

The DEFENDER study (“*Estudo Clínico RanDomizado Avaliando a
Eficácia da DapagliFlozina em Pacientes IntErNaDos em Estado
CRítico*”) was designed to assess the efficacy and safety of
repurposing dapagliflozin for unselected critically ill patients with acute organ
dysfunction.

## METHODS

DEFENDER (ClinicalTrials.gov unique identifier NCT05558098) is an investigator-initiated trial coordinated and
sponsored by the Academic Research Organization (ARO) of the *Hospital
Israelita Albert Einstein*, funded through the *Programa de Apoio
ao Desenvolvimento Institucional do Sistema Único de
Saúde* (PROADI-SUS) from the Brazilian Ministry of Health.

The study coordinating site is responsible for overseeing all trial operations
(start-up activities, regulatory affairs, site management, data management, and
scientific oversight). The steering committee (SC) comprises coordinating center
members and academic leaders responsible for supervising the study’s progress,
monitoring, and considering recommendations from the data monitoring and safety
board (DSMB). SC members will also plan academic publications, draft and review the
study manuscript, and present study results at scientific meetings. To ensure trial
participants’ safety, the DMSB members are independent experts appointed to the
committee, namely, [name] (chair), an intensivist and clinical researcher;
[name], a physiotherapist specialist in intensive care and clinical
trial; and [name], a biostatistician.

The study is being conducted in accordance with Good Clinical Practice guidelines.
Prior to study initiation or implementation of changes, the study protocol and all
amendments will be approved by Ethical Committees at each participating site.
Participants or their legal representatives will provide informed consent before
enrollment. In cases where participants are initially deemed incapable of giving
consent due to impairment in decision-making capacity, consent will be reobtained
after the participant regains capacity during the study follow-up period (e.g.,
after recovery from *delirium*). The informed consent form (ICF)
contains all requirements elements (Resolution 466, 2012) related to research with
human subjects according to the Brazilian National Research Ethics Commission
(Conep) and Good Clinical Practice guidelines. The study design is in accordance
with the Standard Protocol Items: Recommendations for Interventional Trials
(SPIRIT)^(23)^ statement
(Table 1S - Supplementary Material), and the trial registry contains all 24 items
from the World Health Organization Trial Registration DataSet.

### Study objective

The primary objective is to assess whether the use of dapagliflozin in patients
with critical illness and acute organ dysfunction improves the hierarchical
endpoint of hospital mortality, initiation of kidney replacement therapy (KRT)
and hospital length of stay. The secondary objectives are to assess the effect
of dapagliflozin on the individual components of the hierarchical endpoint
(hospital mortality, initiation of KRT and hospital length of stay) and on
patient-centered endpoints (hospitaland intensive care unit-free days and organ
support-free days).

### Study design and population

DEFENDER is an investigator-initiated, multicenter, randomized, open-label, phase
2/3 trial. Eligible participants will be 18 years of age or older, admitted to
an ICU with an expected length of stay > 48 hours in the opinion of the
attending physician, and with at least one organ dysfunction (hypotension, signs
of acute kidney injury, and/or need for new use of a high-flow nasal catheter,
noninvasive or invasive ventilation). Patients will be eligible within 24 hours
after onset of organ dysfunction. Key exclusion criteria are age < 18 years,
pregnancy, end-stage kidney disease on maintenance dialysis, planned ICU
admission after elective surgery, use of dapagliflozin or of other SGLT2
inhibitors, total fasting, and type 1 diabetes mellitus or history of diabetic
ketoacidosis. A full list of the inclusion and exclusion criteria is presented
in table 1. Site investigators and
personnel are encouraged to screen all ICU beds on a daily basis to identify
potential participants.

**Table 1 t1:** Eligibility criteria

Inclusion criteria	
1. Patients admitted to an intensive care unit with expected length of stay of at least 48 hours in the opinion of the attending physician	
2. Patients with at least one organ dysfunction, defined by at least one of the following:	
- Hypotension (mean arterial blood pressure < 65mmHg or systolic blood pressure < 90mmHg or use of vasopressors - norepinephrine, epinephrine, adrenaline, or vasopressin at any dose)	
- Signs of kidney injury: decreased urinary output within the last 6 hours (< 0.5mL/kg/h for the past six hours) or increase in serum creatinine by at least 0.3mg/dL over previous measurement	
- Need for new use of a high-flow nasal catheter, noninvasive or invasive ventilation	
Exclusion criteria	
1. Pregnancy	
2. Age below 18 years	
3. Patient or legal representative refusal to participate	
4. End-stage kidney disease on maintenance dialysis	
5. Planned intensive care admission after elective surgery	
6. Known allergy to dapagliflozin	
7. Previous use of dapagliflozin or of other SGLT2 inhibitor	
8. Total fasting, unable to receive the medication PO or enterally	
9. Patients with inclusion criterion number 2 for more than 24 hours	
10. Type 1 diabetes or history of diabetic ketoacidosis	

SGLT2 - sodium-glucose cotransporter 2 inhibitor; PO - by
mouth.

### Study procedures

#### Interventions

Eligible patients will be randomized 1:1 to dapagliflozin 10mg plus standard
of care or standard care alone (Figure 1). Randomization is performed centrally through the Research
Electronic Data Capture (REDCap) system,^(24)^ stratified by study site with variable
block sizes of 4, 8 and 12. A confidential randomization list was generated
by the coordinating center. As an open-label study, no procedures to blind
site staff, study personnel, or physicians involved in patient care will be
conducted.

**Figure 1 f1:**
[figure not shown]
DEFENDER study design and flow chart.

All study procedures will be performed by site staff. Patients in the
intervention arm will receive dapagliflozin 10mg/day for 14 days (or until
ICU discharge, whichever comes first). Patients in the control arm will
receive a routine standard of care. Dapagliflozin will be started on the day
of randomization, preferably in the morning without fasting, orally for all
participants able to swallow pills. For participants who cannot take oral
medications, dapagliflozin will be administered enterally (orogastric tube,
oroenteral tube, gastrostomy, jejunostomy, as available) after maceration
and dilution in water.

Dapagliflozin should only be withheld in the following situations:

- Requirement for absolute fasting and/or inability to access the
enteral route for the drug.- Occurrence of euglycemic diabetic ketoacidosis, defined by high
anion gap metabolic acidosis and ketone bodies in the urine.- More than one episode of severe hypoglycemia (≤ 50mg/dL)
during drug use.- Withdrawal of consent.- Suspected allergic reaction to dapagliflozin as well as other
idiosyncratic drug reactions, such as DRESS syndrome (drug rash with
eosinophilia and systemic symptoms).- Initiation of kidney replacement therapy.

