#### Monitoring for adverse events

Study sites and investigators will receive specific recommendations on
careful monitoring of blood glucose, acid‒base disorders, and renal function
during the study to minimize SGLT2 inhibitor-related risks. Glycemic control
is to be performed according to the institutional guidelines of each study
site for all participants. The study protocol recommends that participants
should be monitored at least every 6 hours for blood glucose levels using
bedside blood glucose meters or venous/arterial samples until they recover
from all organ dysfunctions. For unstable participants who require
vasopressors or inotropes or are undergoing invasive mechanical ventilation,
blood glucose levels should be monitored at least every 2 hours, but hourly
monitoring is strongly recommended, with a target blood glucose level below
180mg/dL. Management of hyperglycemic episodes should preferably be done
through an intravenous insulin pump for unstable or mechanically ventilated
participants or through intermittent insulin (intravenous or subcutaneous)
for other participants. The minimum daily carbohydrate intake for all
participants was set at 100g of glucose, considering all infusions.
Creatinine levels and blood gas analysis (pH, bicarbonate, anion gap, base
excess) will be monitored daily during the first five days of study
follow-up.

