#### Study follow-up

Participants will be followed for 28 days or until hospital discharge,
whichever is sooner. The intervention group will be assessed for adherence
to the study drug daily from Days 1 to 14. For both the intervention and
control groups, adherence to mandatory laboratory parameters (serum
creatinine and blood gas analysis) will be assessed daily from Days 1 to
5.

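### Read literally, the closed withholding list keeps a patient with unexplained high anion gap acidosis on dapagliflozin until urinary ketones are shown, while a merely suspected allergy is enough to hold it

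*Protocol article*

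**What the plan says.** The rule stands in the Protocol article under Study procedures, Interventions, in the list that follows Figure 1.

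- The list is introduced as exclusive: "Dapagliflozin should only be withheld in the following situations". Six situations follow: no enteral route or absolute fasting, ketoacidosis, repeated severe hypoglycemia, withdrawal of consent, allergy or idiosyncratic reaction, and start of kidney replacement therapy.
- The ketoacidosis item is "Occurrence of euglycemic diabetic ketoacidosis, defined by high anion gap metabolic acidosis and ketone bodies in the urine".
- The allergy item begins "Suspected allergic reaction to dapagliflozin as well as other idiosyncratic drug reactions".
- Treatment is "dapagliflozin 10mg/day for 14 days (or until ICU discharge, whichever comes first".

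Three other places bear on how the rule works:

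- Table 1 (Study design and population) admits patients for, among other things, "decreased urinary output within the last 6 hours (< 0.5mL/kg/h for the past six hours".
- Monitoring for adverse events states: "Creatinine levels and blood gas analysis (pH, bicarbonate, anion gap, base excess) will be monitored daily during the first five days". Ketones are not among the measurements named. The same section opens with "Study sites and investigators will receive specific recommendations on careful monitoring of blood glucose" and extends this to acid-base disorders and renal function. The content of those recommendations is not shown.
- Standard of care leaves treatment decisions to the local team but exempts the study drug.

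**The concern.** The ketoacidosis item is triggered by a confirmed event with two joint laboratory conditions, inside a list that allows no other reasons. The list's author could write a rule based on suspicion and did so for allergy. For ketoacidosis, which the article collects as an adverse event of special interest, suspicion does not suffice.

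The situation at risk is specific. A blood gas shows a high anion gap acidosis with no evident cause. The urine ketone result has not come back, or no urine can be obtained. The next daily dose falls due, and as printed the rule does not let the site hold it. What is at stake is the safety of that participant, in what the article describes as the first study of this drug class in critically ill patients without COVID-19.

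**Working it through.** No figure in the article is at issue. The check is a reading of the rule, followed by an illustration of what the rewording would cost.

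**Step 1: is the list closed?** Yes. Its introduction contains the word only, and no item leaves room for clinical judgement in general. The Standard of care section does not supply an override, because it excludes study medication from what the local team decides.

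**Step 2: what does each item require?** Ketoacidosis requires occurrence, defined by acidosis and urinary ketones together. Allergy requires suspicion.

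**Step 3: apply the rule.** Take a patient with high anion gap acidosis not otherwise explained, to whom none of the other five items applies. The rows are logical cases, not frequencies.

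| Urine ketones | Rule as printed | Rule as reworded below |
|---|---|---|
| Present | Withhold | Withhold |
| Absent | Continue | Continue or resume |
| Result pending when the next dose is due | Continue | Hold until the result |
| Sample not obtainable | Continue | Hold; test blood ketones, then decide |

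The two versions differ only in the last two rows.

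**Step 4: when does the gap bite?** Dosing is once daily. A pending result matters only if it is still outstanding when the next dose is due, so a prompt urine test closes the gap. An unobtainable sample does not resolve in this way. The low-urine-output entry criterion makes that case plausible, although low output is not absence of urine and many such patients can still give a sample.

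**Step 5: what might the rewording cost in doses?** Inputs from the article: 500 participants randomized 1:1, hence 500 / 2 = 250 on dapagliflozin, for up to 14 days. Assumptions, not in the article: 5% to 30% of these patients meet the new trigger once, and each misses one dose.

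- Doses missed: 250 x 0.05 = 12.5, to 250 x 0.30 = 75.
- Share of doses at 14 drug days each (250 x 14 = 3,500): 12.5 / 3,500 = 0.4%, to 75 / 3,500 = 2.1%.
- Share of doses at 7 drug days each (250 x 7 = 1,750): 12.5 / 1,750 = 0.7%, to 75 / 1,750 = 4.3%.

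Prompt results would lower these figures. Slow results or repeated triggers would raise them.

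**The case against.** The strongest reply is that the article condenses a fuller protocol. Sites receive specific recommendations meant to reduce the risks of this drug class, and holding a dose while ketones are checked is the kind of operational detail such material would contain. That stands as a limit, but it does not remove the point. The concern is with a rule that is printed, not with one that is absent. If the recommendations do allow a hold on suspicion, they conflict with the word only, and the printed wording should be aligned with them.

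Second, the difference from the allergy item need not be an inconsistency. Ketoacidosis has a laboratory definition and allergy is given none, so suspicion is a natural word for the latter. Requiring ketones also adds specificity where high anion gap acidosis may be common. This is fair: the choice trades sensitivity for specificity. But specificity is needed to confirm the event, and a temporary hold can rest on less.

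Third, other safeguards exist. Type 1 diabetes and past ketoacidosis are exclusions, a minimum daily carbohydrate intake of 100 g of glucose is set, fasting and kidney replacement therapy are themselves reasons to withhold, and the safety board reviews unblinded data. Also, should is softer than must, and a careful clinician may hold the drug anyway. All of this narrows the exposure and supports a low severity. None of it lets a dose be held in the last two rows of the table.

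**Conclusion.** The point holds as a minor defect in safety wording, with medium confidence. It rests on a literal reading of the list and on the absence, in the text shown, of any provision that overrides it. Its size in patients cannot be derived. The primary outcome, sample size, power and interim harm rule are unaffected.

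A reader might infer more, and the article does not support it:

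- **That the lack of a scheduled ketone test is an error.** The site recommendations are not shown and may cover it.
- **That acid-base surveillance ends while drug continues.** The article says "adherence to mandatory laboratory parameters (serum creatinine and blood gas analysis) will be assessed daily from Days 1 to 5", and drug may run to Day 14, but only the mandatory measurements end then. Anyone still being dosed is in intensive care, where clinically ordered gases may continue.
- **That ketoacidosis counts will be biased between the arms.** The trial is open-label and only one arm has a drug to withhold, so testing could differ. However, the mandatory gases apply to both groups, the event is collected whatever its severity or attributed cause, and nothing in the article gives a size or direction for any bias.

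**What to change.** Reword the ketoacidosis item in the withholding list along these lines: *Suspected or confirmed ketoacidosis. For high anion gap metabolic acidosis not otherwise explained, withhold pending a ketone result. Confirmed by ketones in blood or urine. Resume if negative.*

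Accepting blood ketones removes the dependence on a urine sample. If the site recommendations already say this, only the list needs to be brought into line.

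The cost is a wording change and some once-daily doses held while a result is awaited; Step 5 of the working illustrates the scale under its stated assumptions. Efficacy and safety are analysed by intention to treat, so a held dose removes no patient from the comparison.

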#### Standard of care

Study sites and investigators will be expected to provide optimal management
for critically ill patients according to Brazilian and international
consensus and guidelines. This includes but is not limited to ventilation
support (oxygen, noninvasive ventilation, mechanical ventilation, among
others), hemodynamic support (vasopressors, inotropes), kidney replacement
therapy (hemodialysis, hemofiltration, hemodiafiltration, among others),
deep venous thromboembolism prophylaxis, delirium, sedation, and pain
management. All participant care except for study medication will be solely
determined by the local health care team.

#### Monitoring for adverse events

Study sites and investigators will receive specific recommendations on
careful monitoring of blood glucose, acid‒base disorders, and renal function
during the study to minimize SGLT2 inhibitor-related risks. Glycemic control
is to be performed according to the institutional guidelines of each study
site for all participants. The study protocol recommends that participants
should be monitored at least every 6 hours for blood glucose levels using
bedside blood glucose meters or venous/arterial samples until they recover
from all organ dysfunctions. For unstable participants who require
vasopressors or inotropes or are undergoing invasive mechanical ventilation,
blood glucose levels should be monitored at least every 2 hours, but hourly
monitoring is strongly recommended, with a target blood glucose level below
180mg/dL. Management of hyperglycemic episodes should preferably be done
through an intravenous insulin pump for unstable or mechanically ventilated
participants or through intermittent insulin (intravenous or subcutaneous)
for other participants. The minimum daily carbohydrate intake for all
participants was set at 100g of glucose, considering all infusions.
Creatinine levels and blood gas analysis (pH, bicarbonate, anion gap, base
excess) will be monitored daily during the first five days of study
follow-up.

#### Study follow-up

Participants will be followed for 28 days or until hospital discharge,
whichever is sooner. The intervention group will be assessed for adherence
to the study drug daily from Days 1 to 14. For both the intervention and
control groups, adherence to mandatory laboratory parameters (serum
creatinine and blood gas analysis) will be assessed daily from Days 1 to
5.

#### Data collection and management

Trained research personnel from study sites will use the REDCap system to
collect data. Data on eligibility criteria that are not met will be
collected as screening logs. At randomization, demographic information,
comorbidities, concomitant medications, reason for ICU admission, and
illness severity will be collected. Daily data collection will include
information on treatment adherence, blood gas analysis, and serum
creatinine. Blood gas analysis forms will contain ranges of possible values
for pH, bicarbonate, and base excess. Information regarding study outcomes
will be collected on Day 28 or at hospital discharge. Serious adverse events
and adverse events of special interest will be collected throughout the
study.

To ensure data quality and confidentiality, investigators and study staff
will receive training on data collection, including a dedicated training
environment in the electronic data capture system that will register
deidentified information about study participants. The coordinating center
will check the data weekly, and study sites will receive a monthly report on
data quality. On-site and remote monitoring will be conducted during the
study. We plan to recruit 500 participants in at least 20 Brazilian
ICUs.

